**Methods/design:**

IIBAPPA is a multi-centre randomised non-inferiority trial. Women with a primary post-partum haemorrhage (PPH) >1000 mL and resultant haemoglobin (Hb) 5.5-8.0 g/dL after resuscitation with ongoing symptomatic anaemia who are otherwise stable (no active bleeding) are eligible to participate. Patients with sepsis or conditions necessitating rapid Hb restoration are excluded. Eligible participants are randomised to receive a blood transfusion or a single dose of intravenous iron polymaltose calculated using the Ganzoni formula. Primary outcome measures include Hb, Ferritin and C-Reactive Protein levels on Day 7. Secondary outcomes evaluate (i) Hb, Ferritin and CRP levels on Day 14, 28, (ii) anaemia symptoms on Day 0, 7, 14 and 28 using structured health related quality of life questionnaires, (iii) treatment safety by assessing adverse reactions and infection endpoints and (iv) the quantitative impact of anaemia on breast feeding quality using a hospital designed questionnaire.

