## Background

Post-partum haemorrhage (PPH) commonly complicates pregnancy and can result in acute anaemia [1]. Up to 10% of women with blood loss in excess of 1000 mL will develop severe anaemia (Hb < 8 g/dL), which can be associated with lethargy, decreased mental alertness, physical weakness, poor concentration and a predisposition to post-natal depression [2–4].

Red blood cell (RBC) transfusions have traditionally been used to manage severe anaemia in the pueperium however in the absence of clear transfusion triggers many women without severe symptoms will also receive blood transfusions. This places them at an increased risk of septicaemia, haematological reactions, delayed wound healing and thromboembolism, particularly if they receive multiple transfusions [5]. Blood products are also a scarce and costly resource [5]. Recent institutional guidelines and trial data suggest blood transfusions are likely to be appropriate in patients with Hb < 7 g/dL but not necessarily if alternative therapy is available or if the individual is clinically well compensated [5, 6].

Intravenous (IV) iron therapy has been shown to reduce the requirement for allogenic blood transfusion and can restore haemoglobin levels by an average of 2.5 g/dL at day 5 post infusion with peak effects observed at 3-6 weeks [2, 7–13]. Compared to RBC transfusions, newer iron preparations excluding dextran derivatives are cheap, display a more benign side effect profile than blood transfusions (<0.5% risk of serious adverse events, 1-3% risk of mild adverse events) and have single dosing regimens [14–16].

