### Primary objectives

To determine if intravenous iron is non-inferior to RBC transfusion in correcting haemoglobin deficit, replenishing iron stores and improving clinical symptoms in women with acute post-partum anaemia without increasing the rate of adverse outcomes.

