### Hypothesis

Intravenous iron is non-inferior to RBC transfusion in women with acute post partum anaemia in correcting Hb levels and improving clinical symptoms with no increased rate of adverse outcomes.

Intravenous iron is superior to blood transfusion in replenishing pre-pregnancy iron stores.

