
A new intravenous cannula will be inserted immediately prior to treatment to minimise the risk of cofounding infection.

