### Statistics

To demonstrate equivalence of the interventions in restoring Hb levels at Day 7 with 90% power at 5% significance (α = 0.025), 116 women need to be recruited to each intervention group. Based on similar studies, this assumes an acceptable difference in Hb of 1 g/dL and an expected difference of 0.7 g/dL [2, 8, 12]. Hence, the final sample size, accounting for a 10% loss to follow up, is a total of 250 women.

Participants experiencing adverse reactions will remain in the trial unless they fail to meet inclusion and exclusion criteria at any point. Data will be analysed according to the intention to treat principle. Primary outcomes and secondary binary outcomes will be analysed using one sided and two group t-tests. The incidence of adverse reactions and symptom scores will be assessed by calculating rates and 95% confidence intervals. Validity of the Post Partum Symptom Scale (PPSS) will be determined at the time of analyses as part of an embedded study and if validated, correlations between subscales and primary outcomes will be analysed.

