### Follow up

The follow up period consists of 4 weeks with face-to-face visits at Day 7, 14 and 28. At each of these visits women will be seen by a research midwife or doctor. Hb, ferritin and CRP will be checked and results recorded in the study file. Patients will have been discharged with completed pathology forms to facilitate compliance with follow-up laboratory testing. Women will also undergo a clinical examination following a specified checklist to assess for any features of infection or other adverse outcomes . Symptom scores using the three specified scales will be collected at each of the follow up sessions. Research midwives will make all effort to ensure compliance with follow up and can facilitate home visits, including pathology collections if required.

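### Infection is a named safety endpoint in the abstract and is assessed at every follow-up visit, but the body's outcome list and safety analysis name only adverse reactions, with no between-arm contrast

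*Protocol article*

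**What the plan says.** The protocol article describes safety in several places, and not in the same terms.

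- **Abstract, Methods/design:** the third group of secondary outcomes is "treatment safety by assessing adverse reactions and infection endpoints".
- **Primary objectives:** iron is to be non-inferior "without increasing the rate of adverse outcomes". The **Hypothesis** repeats this: "with no increased rate of adverse outcomes".
- **Interventions:** a fresh cannula is placed just before treatment to "minimise the risk of cofounding infection".
- **Follow up:** at the Day 7, 14 and 28 visits a clinical examination follows a set checklist to "assess for any features of infection or other adverse outcomes".
- **Secondary outcomes:** the only safety item is adverse reactions. Infection does not appear.
- **Statistics:** "The incidence of adverse reactions and symptom scores will be assessed by calculating rates and 95% confidence intervals". No difference, ratio or test between the arms is given for adverse reactions in that sentence.

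**The concern.** The Secondary outcomes and Statistics sections determine what is reported, and both leave out an endpoint that the abstract names. This is not detail lost when a full protocol is condensed: the shorter text has the endpoint and the longer text does not.

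Two things are at stake. First, if infection is not a listed outcome, reporting it becomes a choice made after the results are known, in a trial whose treatments are open-label. Second, the objective and hypothesis claim that iron does not raise the rate of adverse outcomes. A table of reactions alone would mainly describe events around the infusion or transfusion. Separate rates with separate intervals also do not directly estimate the difference that the claim is about. The Discussion anticipates calling iron the safer treatment, so this comparison will carry weight.

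**Working it through.** The point is mainly one of text, so the check sets the sections side by side. The plan has no figure of its own here to reproduce.

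**Step 1. Is infection an outcome?**

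| Section | Adverse reactions | Infection |
|---|---|---|
| Abstract, Methods/design | named | named separately |
| Follow up (Day 7, 14, 28) | not by that term | named, with other adverse outcomes |
| Secondary outcomes | named | absent |
| Statistics, safety sentence | named | absent |

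Infection is announced and assessed, but neither listed nor named for analysis.

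**Step 2. Could adverse reactions already include infection?** The article does not define the term. Its usage points the other way:

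- The abstract joins reactions and infection with *and*, which would be redundant if one contained the other.
- Interventions lists signs watched for during the iron infusion, such as urticaria, bronchospasm and hypotension. It describes slowing or stopping the infusion in response to reactions, which fits only events during administration.
- Monitoring/reporting of data illustrates severe adverse reactions with anaphylaxis and haematological reaction.
- Follow up places infection among adverse *outcomes*, the term that the objective and hypothesis use.

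The natural reading is that reactions exclude infection. It remains an inference from usage.

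**Step 3. Does the analysis match the claim?** The claim is comparative: no increased rate. The safety sentence promises rates and 95% confidence intervals and does not mention a difference between arms.

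**Step 4. What could a comparison show?** The inputs are n = 116 per arm (Statistics) and a common event rate p in both arms. The documents give no infection rate, so p is assumed. The 95% half-width for a risk difference, by the normal approximation, is

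1.96 × √(2p(1 − p)/n)

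| Assumed p | Calculation | Half-width (percentage points) |
|---|---|---|
| 2% | 1.96 × √(2 × 0.02 × 0.98/116) | 3.6 |
| 5% | 1.96 × √(2 × 0.05 × 0.95/116) | 5.6 |
| 10% | 1.96 × √(2 × 0.10 × 0.90/116) | 7.7 |

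At 2% only about 116 × 0.02 = 2.3 events per arm are expected, so the approximation is rough there. These widths show what a comparison can and cannot say. They do not measure the size of the defect.

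**The case against.** The strongest reply has three parts.

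*The article already covers infection.* The abstract names it as a secondary outcome, and Statistics also says that secondary binary outcomes will be compared by t-tests. If infection is scored as present or absent, that sentence could give it a between-arm analysis. This partly stands: one cannot say that infection certainly would go uncompared. But the route depends on taking the outcome from the abstract when the body's own list omits it, so the conflict remains.

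*The terms are loose and undefined.* The article also speaks of adverse effects, serious adverse events and safety endpoints, and the full protocol or analysis plan may define reactions broadly. It is fair that an article need not carry definitions. That does not excuse two sections of the same article giving different outcome lists.

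*The data safety and monitoring board is to consider the difference in serious adverse events between groups.* That is true, but it is a rule for suspending the study and not a final analysis.

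A reader might go further. The Background says that transfusion carries an "increased risk of septicaemia, haematological reactions, delayed wound healing and thromboembolism", and it is tempting to infer that three of these four harms are looked for at every visit and then left out of the comparison. The documents do not support this. Delayed wound healing and thromboembolism appear only there, as background risks. No visit, row of Table 1 or outcome names them, and the checklist is not shown. A risk cited as background is not a promised endpoint. Nor is haematological reaction, the fourth harm, clearly better served, since no between-arm contrast is stated for reactions either.

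**Conclusion.** The concern holds for infection. The abstract and the body disagree on whether it is a safety outcome, although it is assessed at three visits. In addition, the stated safety analysis gives no between-arm contrast for a claim that is comparative and framed in wider terms than the outcome listed.

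This rests on reading adverse reactions as the article uses the term, without a formal definition. It does not establish that infection data would be lost or never compared, and it does not extend to wound healing or thromboembolism as omitted endpoints.

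The correction should be made, but its yield is modest. With 116 women per arm and assumed rates of 2% to 10%, the risk difference would be known to within about 3.6 to 7.7 percentage points either way. That is enough to describe the arms side by side, but not to rule out a moderate increase in infection.

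**What to change.** - **Secondary outcomes:** add infection to Day 28, taken from the existing Day 7, 14 and 28 assessments, as an item beside adverse reactions. This brings the list into line with the abstract.
- **Terms:** state how adverse reactions relate to the adverse outcomes of the objective and hypothesis, and use each term consistently.
- **Statistics:** for adverse reactions and for infection, report the number and proportion of women with at least one event in each randomised arm, and the between-arm risk difference with its 95% confidence interval. Label these comparisons descriptive.
- **Wound healing and thromboembolism:** check the visit checklist. If it already records them, report them in the same way. If it does not, this point gives no ground for adding them.

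The cost is wording in two sections and one more safety table. No visit, examination or treatment rule changes. The downside is that the intervals will be wide, and the text must say that a wide interval including zero is not evidence of equal safety.

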### Procedures, recruitment and randomisation

Table 1 describes the schedule of enrolment, interventions and assessments during the trial.

**Table 1 Tab1:** Schedule for enrolment, interventions and assessments

	Enrolment	Allocation	Post Allocation				Close-out
TIMEPOINT	Feb 2016	At Enrolment	0-48 h	Day 7	Day14	Day 28	Day 28
ENROLMENT:							
Eligibility screen	X						
Informed consent	X						
Randomisation		X					
Intervention/Preparation (pharmacy/blood bank)			X				
INTERVENTIONS:							
RBC Transfusion			X				
Intravenous Iron Polymaltose			X				
ASSESSMENTS:							
E-5D,MFI-20) and PPSS symptom scores			X	X	X	X	
Clinical history and examination	X		X	X	X	X	
Hb	X			X	X	X	
Ferritin	X			X	X	X	
UEC	X						
CRP	X			X	X	X	
Reticulocyte Count	X			X	X	X	
Group and hold	X						
Vital Signs		X		X	X	X	

Clinical staff at all sites will be able to contact the research team at any time to enrol participants. Research midwives at the primary site will identify women from daily birth records who have had a PPH >1000mls. These women will be briefed on the study using a structured information sheet about the trial and interventions. Following this they will verbally consent to preliminary bloods including a group and hold, haemoglobin, creatinine (to exclude acute kidney injury), ferritin and CRP. Eligible patients will then provide written informed consent and be enrolled to participate in the study (intervention and follow up phases).

Participants will be stratified as per mode of delivery and randomisation will occur within these groups by a computer generated list, blocked in a 1:1 ratio to each intervention. A central telephone service will be accessed to allocate the intervention and study identification number.

Eligible women who decline partipation in the trial will be offered 325 mg oral ferrous sulphate daily until iron replete, which is in accordance with current standard practice guidelines. This will be mentioned in the consent process.

Blinding during the intervention stage is practically difficult due to strict hospital protocols requiring bedside checks and regulated transparent packaging for all blood products. During the follow up phase however researchers will be blinded to the participant’s intervention and researchers who enrolled a particular participant will not be allocated to conduct their follow up interviews. Participants are reminded not to disclose their intervention to the researcher during follow up. We acknowledge that strict blinding in this phase may be difficult.

### Data collection

Each participant will have a study file labelled with their name, medical record number, study identification number and allocated treatment. This will contain copies of their consent forms (the original will remain in their hospital file while they are an inpatient), questionnaires and comprehensive study checklists template for documenting outcome variables and other clinical data. Files will be kept in locked cabinets on the ward and in the principle researcher’s office after discharge and remain on site for 7 years before being destroyed/archived.

Baseline blood results (Hb, ferritin, CRP) for all enrolled participants will be manually transcribed by researchers from the hospital electronic database into the participant’s study file. Once allocated to an intervention, the number and coding sticker of each blood unit or the serial number and dose of the pre-packaged iron infusion will be recorded in the template.

Patient symptoms will be scored on Day 0 prior to receiving any intervention using previously validated HRQoL questionnaires: the EuroQol-5D (E-5D), the Multidimensional Fatigue Inventory (MFI-20) and our in-hospital devised Post-Partum Symptom Score (PPSS).

The EQ-5D measures a patient’s activity level and emotional attitude at a single point in time, indirectly reflecting symptom severity. It consists of five items (Mobility, Self-Care, Usual Activities, Pain/Discomfort and Anxiety/Depression) where a patient scores: 1 = no problems, 2 = more problems, 3 = extreme problems. The sixth item is a patient’s own global evaluation of their health using a visual analogue scale with a range from 0 (worst imaginable health state) to 100 (best imaginable health state) [21].

The MFI is a 20-item self-report instrument designed to comprehensively measure fatigue. It evaluates: general, physical and mental fatigue and reduced motivation and activity. Patients score each dimension on a scale ranging from 4 to 20 where 4 is optimal. Hence, higher scores indicate more severe symptoms. Scales are balanced to reduce the influence of response tendencies. Each scale sub-total is interpreted independently. Questions are structured to evaluate symptoms over a period of time (5-7 days) which is particularly useful to measure treatment impacts [22]. Both the MFI and EQ-5D have previously been validated in pilot studies of obstetric cohorts [23].

The PPSS developed by clinicians at Westmead Hospital is a 27 point self-report questionnaire measuring frequency across three subscales: frequency of clinical symptoms commonly observed in anaemic patients (6 questions), feeding status indicated by changes to breastfeeding habits (7 questions) and home factors to quantify the amount of assistance received to care for the newborn (11 questions). Validity of the scale to discern a relationship between anaemia severity, treatment and breast feeding quality will be determined at the time of data analyses through an embedded study.

Prior to analysis data will be de-identified using study identification numbers and transferred from study files into an electronic database by a study researcher and re-checked by a second researcher. The database will be on a separate computer at the primary study site, accessible only by study researchers and statisticians who will sign a confidentiality agreement stipulating the terms of their use of the data.

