## Design

This is a multi-centre prospective, randomised, open-label, non-inferiority trial.

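### The study file carries the allocated treatment, so the paperwork does not protect the stated blinding at follow-up, and the first symptom scores are not guaranteed to precede randomisation

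*Protocol article*

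**What the plan says.** The Design section describes the trial: "This is a multi-centre prospective, randomised, open-label, non-inferiority trial". Treatment is therefore known when it is given, but the blinding paragraph under Procedures, recruitment and randomisation promises masking later: "During the follow up phase however researchers will be blinded to the participant’s intervention". Two measures support that promise. The person who enrolled a woman does not interview her at follow-up, and women are reminded not to reveal their treatment. The paragraph concedes that strict masking may be hard to achieve.

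The Data collection section describes the file: "Each participant will have a study file labelled with their name, medical record number, study identification number and allocated treatment". It places the questionnaires and the outcome checklist template in that file, and says of the same template that "the number and coding sticker of each blood unit or the serial number and dose of the pre-packaged iron infusion will be recorded". The Follow up section then says: "Hb, ferritin and CRP will be checked and results recorded in the study file". The checklist examination and the three symptom scales belong to the same visits.

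On baseline symptoms, Data collection says: "Patient symptoms will be scored on Day 0 prior to receiving any intervention". In Table 1, the row "E-5D,MFI-20) and PPSS symptom scores" has its first mark in the 0-48 h column under Post Allocation. It has none under Enrolment or Allocation. Randomisation is marked under Allocation, and Hb, ferritin, CRP and reticulocyte count each have an Enrolment mark.

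**The concern.** The article states two procedures that do not fit together. One keeps the follow-up researcher unaware of the arm. The other puts the arm on the label of the file that holds that researcher's forms.

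What is at stake is the judgement-based part of the trial: how symptoms are elicited at interview, and whether a finding on examination counts as infection or another adverse outcome. These are not marginal to the trial's claims. The primary objective covers clinical symptoms and adverse outcomes as well as Hb and iron stores, and the abstract makes adoption of intravenous iron depend partly on symptom scores and safety.

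The baseline point is a separate weakness. A score given once a woman knows her arm can be influenced by that knowledge. It is then no longer a pure pre-randomisation covariate, and a contrast that uses it can carry the influence into the estimated effect.

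**Working it through.** The document gives no figure on this point to reproduce, so the check compares the text of its sections and adds a small illustration.

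**1. The blind and the file**

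| Section | What it fixes |
|---|---|
| Procedures, recruitment and randomisation | Follow-up researchers are masked; enrolling and follow-up staff are separated; women are asked not to disclose |
| Data collection | The file label shows the arm; the file contains questionnaires and outcome checklists; the template shows which treatment was given |
| Follow up | Visit laboratory results go into the study file; symptom scales and the checklist examination are done at the same visits |
| Data collection, on database entry | Identifiers are removed only before analysis, which is after the assessments |

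The two safeguards close two routes to unmasking: the assessor's memory of enrolment, and the woman's own words. Neither closes the route through the file. No separate masked follow-up form is described.

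**2. Extent**

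- Planned total 250 women, visits at Day 7, 14 and 28: 250 × 3 = 750 visits at most.
- With the 116 per arm on which the sample size rests: 116 × 2 × 3 = 696 visits.

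**3. Which outcomes are exposed**

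- Hb, ferritin and CRP at Day 7 are laboratory values and are little affected.
- E-5D, MFI-20 and PPSS are answered by the women, who know their arm. The file label matters for these only through the conduct of the interview.
- The examination for infection and adverse outcomes is the assessor's own judgement and is directly exposed.

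**4. Timing of the first symptom scores**

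Table 1 runs Enrolment, Allocation, Post Allocation 0-48 h. Randomisation is in the second of these and the first symptom scores are in the third. The text requires scoring before treatment is received, which a woman scored after the allocation call but before her infusion would satisfy. Table 1 and the text therefore agree with each other, and neither guarantees a pre-randomisation score.

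**5. Illustration of what a shifted baseline would do**

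These inputs are assumptions; none is in the document. Let δ be the between-arm shift in the first score caused by knowing the arm, in SD units. Let ρ be the correlation of first and follow-up scores, with equal SDs and no effect of the shift on the follow-up score itself.

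- Follow-up scores compared alone: bias from this source is 0.
- Change from baseline: bias = −δ.
- Baseline-adjusted comparison: bias ≈ −ρδ.

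| δ | Change score | Adjusted, ρ = 0.3 | Adjusted, ρ = 0.5 | Adjusted, ρ = 0.7 |
|---|---|---|---|---|
| 0.1 | −0.10 | −0.03 | −0.05 | −0.07 |
| 0.2 | −0.20 | −0.06 | −0.10 | −0.14 |
| 0.3 | −0.30 | −0.09 | −0.15 | −0.21 |

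Under these assumptions the distortion is 0.1 to 0.3 SD for change scores and 0.03 to 0.21 SD with adjustment.

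**The case against.** The best defence is that the document does not show an assessor seeing the label. The Follow up sentence is in the passive, names no recorder and mentions only laboratory results. Files are kept in locked cabinets and move to an office after discharge, and some visits may take place at home. The article also declares the trial open-label, separates enrolling from follow-up staff, and admits that strict masking may fail. On the baseline, the Statistics section states no adjustment and no change score; it gives only rates and confidence intervals for symptom scores.

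Much of this stands. A reader might infer that follow-up assessors are in fact unblinded at every visit. The document does not establish that, because it never says that the labelled file is in the assessor's hands. It shows only that the forms are kept in a file that reveals the arm, with nothing described to prevent exposure. The admission about strict masking does not cure this: it follows a sentence about disclosure by participants, whereas the label is the trial's own doing and can be removed.

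A reader might also take the 5-7 day span of the MFI-20 questions, which at Day 0 can reach back before the haemorrhage, as part of the same fault. It applies to both arms alike, creates no difference between them by itself, and contradicts nothing that the article says it will do with the score.

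Relabelling is also not a complete cure. Transfused women go home on oral iron, and a clinical history is taken at each visit, so the arm may still emerge.

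**Conclusion.** The point holds as an inconsistency that leaves the stated blind unprotected. The follow-up interview and the clinical assessment of infection and adverse outcomes are at risk of bias, at up to 750 visits. To say that these outcomes are biased would go further than the document allows, since neither size nor direction can be derived from it. It would also be wrong to read this as a threat to the Day 7 primary outcomes, which are laboratory values, or to expect masked paperwork to remove reporting bias in women who know their treatment.

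The timing of the first symptom scores is a lesser, conditional point. They are not a guaranteed pre-randomisation baseline. This affects the treatment comparison only if they are used as a covariate or in change scores, which the article does not state. The 0.03 to 0.3 SD range above rests wholly on assumed shifts and correlations.

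Both points should be corrected, because the changes cost almost nothing and concern outcomes on which the trial's conclusions partly depend.

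**What to change.** - Label follow-up questionnaires, checklists and result sheets with the study identification number only.
- Keep the allocation and all treatment records, including blood-unit stickers and iron serial numbers and doses, in a separate folder that follow-up assessors cannot reach. State this in Data collection and in the blinding paragraph.
- Collect E-5D, MFI-20 and PPSS after written consent and before the call to the allocation service. Move the first mark of that row in Table 1 to Enrolment, and amend the Day 0 sentence in Data collection to match.

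The cost is a second folder for each woman, which has to be managed and kept linked by study number. No visit, test or questionnaire is added, and nothing changes in treatment.

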### Secondary objectives

To determine if intravenous iron is superior to RBC transfusion in improving the quality of breast-feeding in women with acute post-partum anaemia.

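### The PPSS is the only breastfeeding measure, is called validated before it has been, and is to be judged at analysis partly by its relation to treatment

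*Protocol article*

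**What the plan says.** - **Objective.** Secondary objectives has one item: whether intravenous iron is "superior to RBC transfusion in improving the quality of breast-feeding". The secondary outcomes list breastfeeding quality at Days 7, 14 and 28, with no condition attached.
- **Instrument.** The Abstract (Methods/design) says the trial will evaluate "the quantitative impact of anaemia on breast feeding quality using a hospital designed questionnaire". In Data collection, the only breastfeeding content in any named instrument is the seven-question feeding subscale of the PPSS.
- **Validation status.** Data collection introduces Day 0 scoring as done "using previously validated HRQoL questionnaires" and names EQ-5D, MFI-20 and the PPSS together. Later in the section only MFI and EQ-5D are said to have been validated, and the validity of the PPSS is left to the time of analysis.
- **What the validation must show.** Data collection describes it as "Validity of the scale to discern a relationship between anaemia severity, treatment and breast feeding quality", to be settled through an embedded study.
- **What depends on it.** Statistics says that "if validated, correlations between subscales and primary outcomes will be analysed". The primary outcomes are Hb, ferritin and CRP at Day 7.
- **Length of the scale.** The PPSS "is a 27 point self-report questionnaire", with subscales of 6, 7 and 11 questions.

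**The concern.** A scale should be shown to measure its construct by evidence that does not depend on the effect it will be used to test. Here treatment is named in the relationship the scale must discern, and the relation of treatment to breastfeeding is exactly what the secondary objective tests. The check is embedded and takes place at analysis, which most naturally means the same women with their outcomes in hand.

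Three consequences follow if the relation to treatment is used as evidence of validity:

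- An arm difference on the feeding subscale would count twice, once for the scale and once for iron.
- No arm difference would be uninterpretable, because equal breastfeeding and an insensitive scale look the same. No second breastfeeding instrument can settle it.
- The correlations with Hb would be reported only after a validation that itself looks for a relation with anaemia severity, so weak correlations would tend to go unreported.

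Labelling the PPSS as already validated hides this from the reader.

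**Working it through.** **Step 1: the passages side by side.**

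1. Secondary objectives, the Abstract and Data collection together give one superiority objective on breastfeeding and one instrument for it.
2. The opening description of the PPSS in Data collection conflicts with the later text of that section and with Statistics. Both later places leave its validity to be determined.
3. The condition in Statistics governs the correlations between subscales and primary outcomes. It is not attached to the between-arm feeding comparison. The same paragraph gives symptom scores an unconditional analysis (rates and 95% confidence intervals), and Table 1 and Follow up count the PPSS among the symptom scores.
4. 6 + 7 + 11 = 24 questions, against 27 points.

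**Step 2: size, under assumed criteria.** The protocol states no pass criterion, so there is no figure of its own to reproduce. The criteria below are assumptions. Setting: 116 women per arm (Statistics), normally distributed scores, no true treatment effect on the score, superiority tested at one-sided 0.025, 10,000 simulated trials, Hb unrelated to arm.

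| Assumed criterion for passing | Scales that pass | Of those passing, falsely favour iron | Of all trials, pass and falsely favour iron |
|---|---|---|---|
| Arm difference on the score, p < 0.05 | 5.3% | 47.7% | 2.5% |
| Arm difference or Hb correlation, p < 0.05 | 10.0% | 25.7% | 2.6% |
| Hb correlation only, p < 0.05 | 4.7% | 2.8% | 0.1% |

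The first row is close to one half by construction: every passing scale already shows a two-sided difference, and chance splits the direction. The last column never materially exceeds the nominal 2.5%.

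**Step 3: the Hb criterion when Hb differs by arm.** Statistics expects a 0.7 g/dL difference in Hb and accepts 1 g/dL. The SD implied by 116 per arm is (1 − 0.7) × √(116/2) / (1.960 + 1.282) = 0.3 × 7.616 / 3.242 = 0.70 g/dL. The pooled correlation between arm and Hb is then 0.35 / √(0.35² + 0.70²) = 0.447.

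With no true effect on the score, the test of the pooled Hb correlation and the test of the arm difference are approximately bivariate normal with that correlation. Both exceed 1.96 in absolute value with probability 0.0079, and 0.0079 / 0.05 is about 16%. A simulation of 40,000 trials agrees: 4.9% pass, 15.2% of those show a false two-sided arm difference (nominal 5%), and 0.049 × 0.152 = 0.7% of all trials do both. So a pooled Hb criterion also carries treatment information if Hb differs by arm.

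**Step 4: the correlations.** If passing meant a pooled correlation with Day 7 Hb at p < 0.05 in 232 women (critical t of 1.970 on 230 degrees of freedom), the smallest correlation that could be reported is 1.970 / √(230 + 1.970²) = 0.13 in absolute value. Every reported correlation with Hb would be significant by construction.

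**The case against.** **Scope of the condition.** A reader might infer that the PPSS is analysed only if it is validated, so that the breastfeeding objective could lose its analysis altogether. The text does not support this. The condition covers the correlations with the primary outcomes; breastfeeding quality and the symptom scores are listed without it. This objection stands in full.

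**Error rate.** A reader might also infer that the trial's false-positive rate for superiority is raised. It is not: across all null trials it stays at about 2.6% or less under the one-sided criteria tried. Any inflation is among scales that pass, and its size depends on a criterion the protocol does not give. This too stands.

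**Meaning of the sentence.** The validation sentence can be read as naming the purpose for which the scale is to be validated, without requiring a treatment difference. Nothing says the validators will know the arms, and the criteria may sit in the embedded study's own plan. This is fair, and it makes the circularity conditional. It does not remove the point, because the article names treatment in what the scale must discern and nothing in it rules out the circular reading.

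**Editorial points.** The sentence that groups the PPSS with validated scales also calls it devised in-hospital, and a later sentence credits only the other two. The contradiction is easily seen, but it still needs correcting. On 27 against 24, a point need not be a question, so that item is only a reconciliation.

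**Conclusion.** The point holds in a limited form. Three things rest on the text alone: the only breastfeeding instrument is unvalidated at the start, its status is stated inconsistently, and treatment is named in what its validation must discern.

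The circularity is conditional on the relation to treatment counting as evidence of validity, and on the embedded study using this trial's data, which is the natural reading but is not spelled out. Under those conditions a positive result is self-supporting and a null result cannot be interpreted. The correlations with the primary outcomes face a similar selection through anaemia severity.

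The illustrative size, with no true effect, is about 48% of passing scales falsely favouring iron under an arm-difference criterion. Under a pooled Hb criterion with the planned 0.7 g/dL separation, about 15 to 16% of passing scales show a false difference in either direction. The matching shares of all trials are about 2.5% and 0.7 to 0.8%. The harm is therefore to interpretation and selective reporting, not to overall type I error. This affects a secondary objective; it should be changed, and it does not threaten the Day 7 primary comparison.

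**What to change.** 1. In Data collection and Statistics, remove treatment from the validity criterion. Assess validity blind to arm, using Day 0 data, reliability, and the relation to MFI-20 and EQ-5D. Where follow-up data are used, take correlations within arm, not pooled across arms.
2. State that the between-arm comparison of the feeding subscale and the subscale correlations with the primary outcomes are reported whatever the validation shows, labelled exploratory if the scale fails.
3. In Data collection, stop describing the PPSS as previously validated.
4. Reconcile the 27 points with the 24 listed questions.

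The cost is wording only; no new data are needed. The downside is that results from a weak scale must be reported and cannot be dropped.
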